## Abstract

**Background:**

Cardiovascular disease is the leading cause of morbidity and mortality in the world, including China. Cardiac rehabilitation (CR) has been demonstrated to be beneficial in reducing cardiovascular mortality, myocardial infarction, and cerebrovascular events. This pilot study seeks to assess the feasibility of aerobic-exercise-based CR in Chinese patients with coronary heart disease (CHD) and outcomes of aerobic metabolism capacity and molecular biomarkers.

**Methods/design:**

This study is a single-center, pilot, randomized, controlled study that is currently being carried out at a regional hospital in Shanghai. Forty patients with CHD who underwent percutaneous coronary intervention will be randomly allocated into either the intervention group or control group. Participants in the intervention group will undergo 8 weeks of aerobic exercise with targeted intensity and participants in the control group will undergo 8 weeks of leisure exercise. The primary measurement is the feasibility of the trial; the secondary measurement is the capacity of aerobic metabolism and the exploratory measurement includes additional molecular biomarkers underlying cardiovascular function.

**Discussion:**

This is the first prospective randomized and controlled clinical study in China that assesses the parameters of aerobic metabolism and comprehensively screens for substantial blood biomarkers to reveal the molecular mechanisms underlying changes in cardiovascular function after aerobic exercise with targeted intensity in participants with CHD. The success of this study will contribute to guide the design of future CR studies in patients with CHD in China.

**Trial registration:**

Chinese Clinical Trial Registry, ChiCTR-IPR-17010556. Registered on 1 June 2016.

**Electronic supplementary material:**

The online version of this article (10.1186/s13063-018-2771-8) contains supplementary material, which is available to authorized users.

## Background

Cardiovascular disease (CVD) is the leading cause of morbidity and mortality in the world [1]. It is not only the top cause of morbidity but also accounts for more than 40% of all deaths because of the continuous increase in the incidence of CVD due to lifestyle changes, urbanization, and an accelerated rate of aging after rapid economic growth over the past 30 years in China [2, 3]. The rising number of CVD deaths in China is largely due to the significant increase in ischemic heart disease, also known as coronary heart disease (CHD), which has been shown to be preventable [2, 4]. Therefore, prevention and control of CHD in China, a country with almost one fifth of the world’s population, may have a significant impact on efforts to achieve sustainable global reductions in CVD rates.

Cardiac rehabilitation (CR), a multifaceted intervention program, has been shown to reduce cardiovascular mortality, myocardial infarction, and cerebrovascular events [5]. It is designed to help patients with CVD achieve optimal physical, psychological, and social status. CR helps to stabilize, slow, or even reverse the progression of the underlying atherosclerotic processes, thereby reducing morbidity and mortality [6, 7]. A large study involving over 600,000 American patients with coronary disease showed that participants undergoing high-dose CR (25 or more sessions) had a lower mortality rate than those undergoing low-dose CR (1–24 sessions) within 5 years of discharge from hospital [8]. CR has been shown to be the third most cost-effective intervention after aspirin and beta blockers to reduce cardiovascular mortality [9]. Moreover, a recent study showed that 3 months of CR, which served as a non-pharmacological way to inhibit platelets, significantly decreased platelet hyperactivity [10].

Although the optimal exercise characteristics (type, dosage, and intensity) that yield the most beneficial effects in patients with CHD are still controversial [11], growing evidence suggests that higher intensity interval training is more effective than lower intensity continuous training for improving aerobic capacity in patients with CHD [12]. This finding is consistent with our previous findings that aerobic exercise with targeted intensity can improve aerobic metabolic capacity in patients who have had a stroke [13]. Markers of aerobic metabolism along with other cardiovascular biomarkers such as C-reactive protein, brain natriuretic peptide, and vascular endothelial growth factor B are important predictors of cardiovascular health or risk [14–16]. Nevertheless, changes in cardiovascular biomarkers after CR have never been investigated comprehensively.

Here, we designed a pilot, randomized, controlled trial to assess the feasibility of aerobic-exercise-based CR on aerobic metabolic capacity and substantial cardiovascular biomarkers in patients with CHD after percutaneous coronary intervention (PCI). The completion of this pilot study will address aspects of feasibility and key issues of uncertainty to promote future pivotal research in generalizing the CR program in China.

## Methods/design

### Aim

The purpose of this pilot study is to test the feasibility of testing the effect of aerobic-exercise-based CR on aerobic capacity and underlying cardiovascular function expressed by molecular biomarkers in patients with CHD after PCI.

### Design

This pilot study is a single-center, prospective, randomized, and controlled clinical trial that will be carried out in the Department of Rehabilitation, Shanghai Xuhui Central Hospital, between 1 June 2016 and 31 June 2018.

All aspects of the study design and protocol adhere to Standard Protocol Items: Recommendations for Interventional Trials (SPIRIT) guidelines (Additional file 1) [17] and will be reported according to the Consolidated Standards of Reporting Trials (CONSORT) statement (Additional file 2) [18]. The protocol has been reviewed and approved by the Ethics Committee of Shanghai Xuhui Central Hospital (approval number 2016–10). The research team of this study will ensure that the ethics standards are adhered to during the study procedure and that they are in accordance with The Code of Ethics of the World Medical Association (Declaration of Helsinki). Participation will be voluntary, and participants can withdraw from the study at any time without any negative consequences. Written consent forms (Additional file 3) and data collected from participants will be kept anonymous and confidential.

### Participant recruitment

A booklet containing basic information about aerobic-exercise-based CR (Table 1) will be distributed to patients registered for PCI in Shanghai Xuhui Central Hospital. Eligible patients who meet the inclusion criteria will be recruited from the Department of Cardiology at the time of discharge after PCI to participate in the CR program conducted in the Department of Rehabilitation.

**Table 1 Tab1:** A booklet containing information on cardiac rehabilitation

List of information related to cardiac rehabilitation	
∙ What cardiac rehabilitation is	
∙ Why patients with cardiovascular diseases need cardiac rehabilitation	
∙ What cardiopulmonary exercise testing is	
∙ Who can take part in the aerobic exercise-based cardiac rehabilitation	
∙ What individualized exercise prescription is	
∙ A brief introduction to the Department of Rehabilitation in Shanghai Xuhui Central Hospital	

The inclusion criteria are as follows: (1) diagnosis of CHD by a cardiologist based on the combination of clinical symptoms and findings on electrocardiogram and/or echocardiogram and/or coronary angiogram; (2) age between 45 and 80 years; (3) low to moderate risk of cardiovascular event posed by participating in CR based on the Chinese cardiac risk stratification as determined by the experts [19]; and (4) provision of a signed consent form. Strict exclusion criteria are used to avoid unexpected adverse events during rehabilitation training, and these are summarized in Table 2.

**Table 2 Tab2:** Exclusion criteria for the cardiac rehabilitation program

∙ Cognitive impairment or mental disorder identified by MMSE score < 24	
∙ Unstable angina or onset of myocardial infarction within < 2 weeks	
∙ Uncontrolled serious arrhythmia	
∙ Uncontrolled hypertension (resting systolic blood pressure > 160 mmHg or resting diastolic blood pressure > 100 mmHg)	
∙ Cardiac function class IV	
∙ Coronary heart disease accompanied by acute complications (coronary artery dissection, ventricular aneurysm, large area of myocardial infarction associated with shock, acute vascular occlusion including stent thrombosis) and high risk of cardiovascular events posed by rehabilitation exercise	
∙ Active pericarditis or myocarditis, serious infection, chronic obstructive pulmonary disease, moderate to serious aortic stenosis, resting heart rate after drug control > 100 times/min	
∙ New deep vein thrombosis, thrombophlebitis, aortic dissection or aneurysm in other parts of the body, lower limb occlusive atherosclerosis	
∙ Inability to tolerate exercise due to fracture, arthritis or muscle pain	
∙ Abnormal electrolytes such as potassium, sodium or calcium	
∙ Uncontrolled hyperthyroidism or hypothyroidism at the time of recruitment	
∙ COPD with signs of infection such as fever, sore throat, coughing, etc.	

*COPD* chronic obstructive pulmonary disease, *MMSE* mini-mental state examination

### Randomization

Participants will be randomly allocated (1:1 ratio) to either the intervention or control group once screening assessments are completed and eligibility for the study is confirmed (Fig. 1). A research coordinator will generate the random allocation sequence, enroll participants, and assign participants to interventions. A stratified randomization scheme based on gender will be used. Microsoft Excel Formula Rand will be used to allocate patients to the intervention or control group. A random number between 0 and 1 will be generated for each patient; if the last digit is an even number the patient will be assigned to group A (intervention) and if the last digit is an odd number the patient will be assigned to group B (control) (Table 3). Forty participants will be allocated randomly to group A (intervention exercise group with targeted intensity, *n* = 20) or B (control group with leisure exercise, *n* = 20).

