**Fig. 1 Fig1:**
[figure not shown]
Study flow chart. Eligible participants with coronary heart disease (CHD) after percutaneous coronary intervention (PCI) will be randomly allocated to the intervention or control group. The exercise intervention is an outpatient clinical rehabilitation program with targeted intensity, which includes a 30-min session three times a week for 8 weeks. Participants in the control group will be prescribed the same number of exercise sessions without targeted intensity. Cardiopulmonary exercise testing will be performed before and after the 8-week cardiac rehabilitation program to assess changes in cardiopulmonary function

**Table 3 Tab3:** A stratified randomization scheme based on gender

Male			Female		
Serial number	Random number	Group	Serial number	Random number	Group
1	0.699718	A	1	0.299478	A
2	0.474505	B	2	0.228082	A
3	0.278238	A	3	0.905825	B
4	0.063581	B	4	0.288985	B
5	0.543526	A	5	0.204267	B
6	0.645542	A	6	0.004536	A
7	0.606382	A	7	0.876704	A
8	0.358782	A	8	0.765598	A
9	0.913533	B	9	0.989875	B
10	0.394207	B	10	0.735247	B
11	0.101518	A	11	0.968638	A
12	0.830019	B	12	0.975038	A
13	0.454501	B	13	0.355564	A
14	0.941391	B	14	0.730377	B
15	0.748873	B	15	0.087323	B
16	0.736089	B	16	0.318215	B
17	0.026114	A	17	0.794593	B
18	0.294124	A	18	0.322396	A
19	0.801002	A	19	0.180908	A
20	0.448855	B	20	0.552161	B

Microsoft Excel Rand is performed to generate random numbers between 0 and 1, last digit even number for group A (intervention) and odd for group B (control). Patients are then allocated to intervention and control groups chronologically

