### Sample size determination

Given the pilot nature of this trial, we will focus on the feasibility of the study and ensure that the exercise intervention runs smoothly, we will not calculate a sample size to determine the power in this study [20]. However, it is recommended that a minimum of 30 participants is required to achieve sufficient precision to enable sample size calculation for subsequent studies [21]. Therefore, we plan to recruit 40 participants, which will allow the completion of data collection from 30 subjects, with a 75% participant retention rate.

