### Trial status

This is an ongoing trial. We have not completed patient recruitment at the time of submission. So far, 13 patients have been enrolled, with 6 in the intervention group and 7 in the control group.

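### One coordinator generates the sequence, enrols and assigns from a fixed list, so allocation is not concealed; the printed list also cannot produce the reported 6/7 split

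*Protocol article*

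**What the plan says.** The Randomization section of the protocol article names one role for every step: "A research coordinator will generate the random allocation sequence, enroll participants, and assign participants to interventions". It places allocation after screening: "Participants will be randomly allocated (1:1 ratio) to either the intervention or control group once screening assessments are completed". It also sets the stratification: "A stratified randomization scheme based on gender will be used".

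Table 3 lists serial numbers 1 to 20 for men and 1 to 20 for women, each with a random number and the resulting group. An even last digit means A (intervention) and an odd one means B (control). The footnote says how the list is used: "Patients are then allocated to intervention and control groups chronologically".

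The Trial status section reports: "We have not completed patient recruitment at the time of submission". It continues: "So far, 13 patients have been enrolled, with 6 in the intervention group and 7 in the control group".

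The article mentions no sealed envelopes, central service or independent list holder. The limitations in the Discussion cover unblinded outcome assessment but not concealment.

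**The concern.** Concealment means that whoever decides on a patient's entry cannot know the arm that patient would receive. Here the person who enrols has made the list and also applies it. A fuller protocol could not easily cure this, because the stated roles leave nobody from whom the list is withheld.

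Foreknowledge leaves room to approach, delay or discourage a patient according to the next arm. Patients seen as fitter or more willing to attend could be steered towards supervised exercise, or away from it. That could bias the between-group changes in AnT, the clinical and laboratory indicators and the biomarkers, which the Data assessment section compares with 95% confidence intervals. It could also distort retention by arm. Outcome assessment of metabolism and clinical indicators is unblinded as well, so sound allocation matters more. Analysis cannot repair lost concealment afterwards.

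**Working it through.** **Inputs.** Target of 40, 30 completers and 75% retention (Sample size determination); 13 enrolled, 6 intervention and 7 control (Trial status); the 40 rows of Table 3.

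**1. The plan's own figures.** The target reproduces: 30 / 0.75 = 40. All 40 rows of Table 3 obey the last-digit rule. The counts are 10 A and 10 B for men, and 10 A and 10 B for women, so 20 and 20 overall, as stated.

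**2. Patients outstanding at submission.** 40 − 13 = 27, and 27/40 = 67.5%. This takes enrolled to mean randomised, which the reported split by group supports.

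**3. Is the list fixed in advance?** The text says that a random number is generated for each patient, which could suggest generation at entry. However, Table 3 already holds all 40 results when 13 patients have entered, and its footnote says it is used in order. It is presented as a fixed list.

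**4. Does Table 3 give the reported split?** Let k be the number of men among the first 13, so that 13 − k are women. The number in A is (A among the first k male entries) + (A among the first 13 − k female entries).

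| Men | Women | A | B |
|---|---|---|---|
| 0 | 13 | 0 + 8 = 8 | 5 |
| 1 | 12 | 1 + 7 = 8 | 5 |
| 2 | 11 | 1 + 6 = 7 | 6 |
| 3 | 10 | 2 + 5 = 7 | 6 |
| 4 | 9 | 2 + 5 = 7 | 6 |
| 5 | 8 | 3 + 5 = 8 | 5 |
| 6 | 7 | 4 + 4 = 8 | 5 |
| 7 | 6 | 5 + 3 = 8 | 5 |
| 8 | 5 | 6 + 2 = 8 | 5 |
| 9 | 4 | 6 + 2 = 8 | 5 |
| 10 | 3 | 6 + 2 = 8 | 5 |
| 11 | 2 | 7 + 2 = 9 | 4 |
| 12 | 1 | 7 + 1 = 8 | 5 |
| 13 | 0 | 7 + 0 = 7 | 6 |

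All 14 splits give 7 to 9 in A and 4 to 6 in B. None gives 6 and 7. Either another list is in use, or assignments departed from Table 3, or the 13 omit some randomised patients. The article does not say which.

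**5. Who could read the next arm from Table 3?** If it is the working list, anyone who knows the running count of men and women can. The Trial status section gives counts by arm only, so an outside reader lacks that information. Each list stops at 20, so it covers all 40 patients only if exactly 20 men and 20 women enter, and no cap by gender is stated.

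**The case against.** The best defence is that the coordinator's discretion is narrow. A cardiologist makes the diagnosis, experts set the risk class, a physician confirms stable vital signs, and allocation follows confirmed eligibility. The article does not say whether the stability check comes before randomisation, so it cannot be assumed to be a point where patients are steered. This stands as a limit on the size of the risk. It does not remove the risk, because the coordinator still enrols, and can influence who is approached and when, while knowing the sequence.

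A second defence is that this is a feasibility pilot. A reader might infer that the primary outcome is compromised. The documents do not support that: the criteria in Data assessment (40 recruited, 75% retention, all outcomes measured in 90% of participants) are not defined by arm, and moving patients between arms mainly redistributes retention. The between-group comparisons are described as exploratory and unpowered, but small size does not protect them from bias.

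A reader might also infer that anyone can predict each of the remaining 27 assignments with certainty. That fails too. Table 3 does not reproduce the first 13 assignments, an outsider lacks the running count by gender, and the lists stop at 20 per gender. Nor does the article show that 27 patients were outstanding when Table 3 became public. The figure belongs to the date of submission, and fewer may have remained at publication.

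**Conclusion.** The point holds. As written, allocation is not concealed, because one role makes the list, enrols and assigns. This does not depend on whether Table 3 was published or is the working list. It applied to 27 of 40 allocations (67.5%) still to be made at submission, and to the 13 already made.

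The mismatch between Table 3 and the 6/7 split is a separate, checkable inconsistency. It assumes that the list is followed in order within gender and that the 13 are all the patients randomised. It may tempt a reader to infer manipulation, but an unpublished replacement list or an incomplete count would explain it equally well.

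The bias is possible, not demonstrated; its direction and size cannot be computed from the article. It bears on the secondary and exploratory comparisons and on retention by arm, and hardly on the overall feasibility criteria.

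**What to change.** For patients not yet randomised:

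- Have an existing colleague outside recruitment and outcome assessment generate and hold a new list stratified by gender. The coordinator continues to enrol but does not see it.
- Conceal it in sequentially numbered, opaque, sealed envelopes for each gender, or an equivalent. Open each one only after eligibility and consent are recorded.
- Do not publish the new list until recruitment closes.

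For patients already allocated, reconcile Table 3 with the 6/7 split, say which list was used, and report these patients as allocated without concealment. Add the point to the limitations.

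The cost is a short amendment and a small amount of a colleague's time.

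### The even/odd rule with two fixed 20-row lists does not ensure the stated 20 per arm or gender balance, and Table 3 does not reproduce the reported 6:7 allocation

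*Protocol article*

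**What the plan says.** All of this is in the protocol article.

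- **Randomization** sets the ratio: "Participants will be randomly allocated (1:1 ratio) to either the intervention or control group". It adds "A stratified randomization scheme based on gender will be used" and fixes the arm sizes: "Forty participants will be allocated randomly to group A (intervention exercise group with targeted intensity, *n* = 20) or B", with 20 in B as well.
- The same section gives the mechanism: "A random number between 0 and 1 will be generated for each patient". An even last digit means group A (intervention) and an odd one means group B (control). No block, cap or other restriction is mentioned. One research coordinator generates the sequence, enrols patients and assigns them.
- **Table 3** prints serial numbers 1 to 20 for men and 1 to 20 for women. Its footnote says how they are used: "Patients are then allocated to intervention and control groups chronologically".
- **Sample size determination** sets one overall target, "Therefore, we plan to recruit 40 participants", with no number per gender.
- **Trial status** reports 13 enrolled so far: 6 in the intervention group and 7 in the control group.

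**The concern.** Two stated properties, 20 per arm and balance by gender, do not follow from the stated rule. Stratification helps only when allocation inside each stratum is restricted, for example by blocks. Independent draws within men and within women have the same distribution as independent draws in everyone.

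The fixed list length adds a second difficulty. Forty rows in two lists of 20 can place 40 patients only when the gender mix is exactly 20 and 20. With any other mix one list runs out, the other stops part-way, and staff must improvise.

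At stake are a mismatch between the stated and the delivered design, and some avoidable imbalance in the planned between-group comparisons. The reported running total also bears on whether the printed list is the one in use.

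**Working it through.** **Inputs.** 40 patients, 20 per arm, even/odd rule (Randomization); 20 rows per gender, used in order (Table 3); 13 enrolled, 6:7 (Trial status).

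**1. The plan's own figure.** All 40 printed groups agree with the parity of the last digit. In order:

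- Men: A B A B A A A A B B A B B B B B A A A B, which is 10 A and 10 B.
- Women: A A B B B A A A B B A A A B B B B A A B, which is 10 A and 10 B.

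Total 20:20, so the stated split is reproduced if both lists are used to the end.

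**2. The rule alone, before any list is drawn.** P(20:20 of 40) = C(40,20)/2^40 = 0.125. P(10:10 in one list) = C(20,10)/2^20 = 0.176. P(10:10 in both) = 0.176² = 0.031.

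**3. When the printed lists suffice.** 40 patients fit into 20 + 20 rows only with 20 men and 20 women. The article gives no gender shares. If 50%, 60% or 70% of recruits were men (assumed), P(exactly 20 men of 40) = C(40,20) p^20 (1−p)^20 = 0.125, 0.055 or 0.004.

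**4. Other mixes.** Assume that the exhausted list is extended by the same even/odd rule. Let *a* be the number of A already fixed by the printed rows used, and *e* the number of patients beyond row 20. Then P(20:20) = C(e, 20−a)/2^e.

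| Men/women | A:B in printed women rows used | *a* | *e* | P(20:20) | Possible A total | P(17:23 or worse) |
|---|---|---|---|---|---|---|
| 22/18 | 9:9 | 19 | 2 | 2/4 = 0.50 | 19–21 | 0 |
| 25/15 | 8:7 | 18 | 5 | 10/32 = 0.31 | 18–23 | 1/32 = 0.03 |
| 28/12 | 7:5 | 17 | 8 | 56/256 = 0.22 | 17–25 | (1+28+8+1)/256 = 0.15 |

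**5. Imbalance inside the printed lists.** The largest A−B difference is 4 in men (6:2 after 8) and 3 in women (8:5 after 13). Before row 20, men are level after 2, 4, 14 and 18, and women after 4, 6, 10, 16 and 18.

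**6. Cost in precision.** With equal outcome variance, the variance of a difference is proportional to 1/n_A + 1/n_B. For 20:20 this is 0.1000. For 17:23 it is 1/17 + 1/23 = 0.1023, so the interval is √1.023 = 1.011 times as wide, about 1% wider.

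**7. The reported 6:7.** Take *m* men and 13−*m* women, each read in order from Table 3. The number in A for *m* = 0 to 13 is 8, 8, 7, 7, 7, 8, 8, 8, 8, 8, 8, 9, 8, 7. It is never 6.

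**The case against.** The other side has a good case on size. The article already prints the lists, and both finish level, so each completed list behaves like one block of 20. A reader might take the 12.5% chance of 20:20 in step 2 as this trial's chance, but it applies before a list is drawn. With the printed lists, 17:23 or worse cannot occur for 17 to 24 men. Likewise, 8 men and 13 women would give 6:2 plus 8:5, or 14:7, but that is the worst interim point, at 21 patients, and not an outcome at 40.

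Feasibility is the primary outcome, and the Data assessment section says that the trial is not powered for effects. No feasibility criterion depends on arm balance. Simple randomisation is valid and is the least predictable method. All of this stands, and it limits the consequence.

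Three stronger readings are not supported:

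- That the scheme can never give 20:20. Once a list is extended, 20:20 can arise by chance.
- That there is a hidden gender quota. Nothing in the article states or implies one.
- That two lists of exactly 10:10 (a 3.1% event), or the 6:7 discrepancy, show that the sequence was chosen or overridden. Chance, an unstated restriction, a different working list, or allocated patients not counted as enrolled would each explain one or the other. The article does not say which.

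It can also be said that a condensed article may omit the rule for extending a list. But this article states the algorithm and prints the whole list, and what it prints does not secure what it promises.

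**Conclusion.** The point holds as a mismatch between stated properties and stated method. The even/odd rule does not ensure 20 per arm or balance by gender, and the printed lists guarantee 20:20 only with exactly 20 men and 20 women. For the other mixes tabulated, the chance of 20:20 lies between 0.22 and 0.50, and 17:23 or worse reaches about 15% at 28 men and 12 women. These figures assume that the printed lists are used in order and the exhausted one is extended by the same rule.

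The effect on precision is about 1% in interval width at 17:23, and the feasibility conclusions are untouched. The scheme should be corrected because that is cheap and recruitment was still open when the article was submitted, not because the trial's validity is threatened.

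The 6:7 discrepancy is a separate matter of record. If Table 3 is the list in use and every enrolled patient has been allocated from it in order, group A should hold 7 to 9 of the first 13. The two passages must be reconciled.

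**What to change.** 1. **Reconcile** Table 3 with the reported 6:7. State which list is in use and whether any allocated patient is missing from the count of 13.
2. **For the remaining 40 − 13 = 27 patients**, use permuted blocks of randomly varying size (for example 4 and 6) within each gender. Give each list at least 27 rows, so that neither can run out whatever the mix. If more patients have since been allocated, start from the number then remaining.
3. **Move the list.** Someone already on the project who does not enrol patients, for example the independent statistician, should generate and hold it. Concealing block sizes cannot work while one coordinator generates the list, enrols and assigns.
4. **State about 20 per group.** Blocks bound the imbalance but do not guarantee 20:20. Among the new allocations, the A−B difference within a gender is at most half the largest block: 2 with blocks of 4, and 3 with blocks up to 6.

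The cost is a short script, an amendment sentence and a change of one role. The downside is slight predictability at the end of a block, which varying the sizes and separating the roles keep small.
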